**Methods and analysis:**

REACT-AVB is a multicentre, randomised controlled, open-label, superiority, two-arm, parallel-group trial with an internal pilot. The two interventions allocated randomly 1:1 are early TIPSS within 4 days of diagnostic endoscopy or secondary prophylaxis with endoscopic therapy in combination with non-selective beta blockers. Patients aged ≥18 years with cirrhosis and Child-Pugh Score 7–13 presenting with AVB with endoscopic haemostasis are eligible for inclusion. The primary outcome is transplant-free survival at 1 year post randomisation. Secondary endpoints include transplant-free survival at 6 weeks, rebleeding, serious adverse events, other complications of cirrhosis, Child-Pugh and Model For End-Stage Liver Disease (MELD) scores at 6 and 12 months, health-related quality of life, use of healthcare resources, cost-effectiveness and use of cross-over therapies. The sample size is 294 patients over a 4-year recruitment period, across 30 hospitals in the UK.

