## Methods and analysis

### Randomised controlled trial of EArly transjugular intrahepatiC porTosystemic stent–shunt in AVB (REACT-AVB) trial design

REACT-AVB is a pragmatic, multicentre, randomised controlled, open-label, two-arm, superiority, parallel group trial with an internal pilot. At least 30 acute NHS trusts/health boards in the UK offering 24-hour service for patients with AVB will be involved in trial recruitment. The detailed trial design is described below.

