#### Standard care arm

Participants will undergo secondary prophylaxis against variceal rebleeding which usually comprises a combination of VBL and non-selective beta blocker (NSBB) as per the BSG guidelines.^3^ Modification (in line with local practice) may be needed due to intolerance of therapies, patient choice with regards to NSBB and banding or serious adverse event (SAEs).

Adherence to standard care will be defined as a participant not receiving early TIPSS within 10 days of diagnostic endoscopy for any indication. If participants in the standard of care arm do receive TIPSS, the reasons for this will be captured on a REACT-AVB CRF. The indications include rescue or salvage TIPSS, refractory or recurrent ascites and secondary prevention against variceal rebleeding.

Both treatments are currently in use in normal clinical practice and therefore the participant will continue to be treated after the trial has ended as per the standard care pathway.

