#### Secondary outcomes

Transplant-free survival at 6 weeks (post randomisation).Rebleeding (Rebleeding is defined as haematemesis and/or melena with either: (1) endoscopic evidence of variceal bleeding or stigmata of recent haemorrhage and at least a 2 g/L reduction in haemoglobin within 24 hours of admission or (2) massive upper gastrointestinal bleeding leading to death. The definition includes bleeding from banding ulceration.) (post randomisation):Early (less than or equal to 6 weeks).Late (greater than 6 weeks).Serious adverse events related to treatment (up to 12 months post randomisation).Other complications of cirrhosis (up to 12 months post randomisation; composite outcome and individual components):New onset ascites.New onset encephalopathy. (Hepatic encephalopathy will be assessed according to West Haven criteria as the most severe grade.^28^ The number of episodes of hepatic encephalopathy will be recorded in follow-up CRFs. Covert or minimal hepatic encephalopathy will be assessed using the animal naming test where less than 20 animals named in 1 min is highly suggestive of minimal or covert hepatic encephalopathy.^28^)Spontaneous bacterial peritonitis.Hepatocellular carcinoma.Any renal dysfunction.Child-Pugh Score at 6 and 12 months post randomisation.MELD Score at 6 and 12 months post randomisation.Cross-over therapies.Health-related quality of life (EQ-5D-5L) at 6 and 12 months post randomisation.Use of healthcare resources, costs and cost-effectiveness based on cost per quality-adjusted life-year (QALY) estimated using the EQ-5D-5L and cost per life year gained at 1 year and modelled cost per QALY over patient lifetime.

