### Schedule of assessments

Schedule of assessments is detailed in table 1.

**Table 1 T1:** Schedule of assessments

Assessment	Eligibility and randomisation	Baseline	2–7 days (TIPSS arm only)	6 weeks±7 days	6 months±7 days	12 months±7 days
Inclusion criteria*	x					
Exclusion criteria*	x					
Seek informed consent	x					
Relevant medical history taken	x					
Concomitant medication		x		x	x	x
Randomisation	x					
Full blood count		x		x	x	x
TIPSS procedure under fluoroscopic guidance†		x				
Renal function		x		x	x	x
Clotting profile	x			x	x	x
Liver function	x			x	x	x
Diagnostic endoscopy	x					
Standard clinical examination		x		x	x	x
Doppler ultrasound	x		x		x	x
Safety reporting		x	x	x	x	x
Quality of life questionnaires (EQ-5D-5L)		x			x	x
Child-Pugh Score ‡	x				x	x
MELD Score		x			x	x

Color significance HIghlight the assessment variable.

*Refer to text for inclusion and exclusion criteria.

†Early TIPSS arm only.

‡Child-Pugh Score is a minimisation variable.

EQ-5D-5L, EuroQol-5 Dimension-5 Level; MELD, Model For End-Stage Liver Disease; TIPSS, transjugular intrahepatic portosystemic stent–shunt.

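### The listed SAE outcome counts only treatment-related events in an open-label trial, so this one secondary comparison is open to attribution bias of unknown size and direction

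*Protocol article*

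**What the plan says.** All references are to the protocol article.

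- **Secondary outcomes** lists "Serious adverse events related to treatment (up to 12 months post randomisation"). This is the only SAE outcome named.
- **Abstract, Methods and analysis** gives the secondary endpoints as including "rebleeding, serious adverse events, other complications of cirrhosis", with no mention of relatedness.
- **Secondary objectives** makes safety one of the things to be compared between early TIPSS and standard of care.
- **Trial design**: "REACT-AVB is a pragmatic, multicentre, randomised controlled, open-label, two-arm, superiority, parallel group trial with an internal pilot".
- **Standard care arm**: control treatment "usually comprises a combination of VBL and non-selective beta blocker (NSBB"), and may be modified for intolerance, patient choice or SAEs.
- **Schedule of assessments, Table 1** has a column headed "2–7 days (TIPSS arm only"). Two rows are marked in it: Doppler ultrasound and "Safety reporting". In the control arm safety reporting is marked at baseline and next at 6 weeks. From 6 weeks on, the two arms have the same safety schedule.
- **Secondary outcomes** also lists harms with no relatedness condition: "Other complications of cirrhosis (up to 12 months post randomisation; composite outcome and individual components"), and rebleeding, of which it says "The definition includes bleeding from banding ulceration".

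**The concern.** A count of related SAEs is filtered by a causality judgement. Here the people making it know the allocation, and the question is not the same in each arm. After TIPSS there is a dated procedure to which an event can be tied. Under standard care there is a continuing course of banding and beta-blockers, and an event may more readily be put down to the underlying cirrhosis. If the fraction of SAEs called related differs by arm, the counts differ even when the true SAE risks are equal.

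The early safety schedule raises a second, smaller question. The article itself stresses the first 5 days after a bleed as a period of particular risk, yet only one arm has a scheduled safety report at 2–7 days.

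At stake is the SAE comparison that would be set beside any survival gain. Some serious events, such as sepsis other than spontaneous bacterial peritonitis, cardiac events, or serious worsening of ascites or encephalopathy already present at entry, are not named among the other clinical outcomes. They would enter the listed SAE outcome only if judged related.

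**Working it through.** **What can be checked directly.** Side by side, the abstract and the outcome list describe different counts: all SAEs, and the subset judged related. Table 1 confirms that the 2–7 day safety report is TIPSS-only. The article gives no SAE rate, attribution rate or capture rate, so there is no figure of the plan's own to reproduce for this outcome.

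**Arm size used below.** The stated 147 per arm does reproduce. HR = ln(0.8)/ln(0.6) = 0.437, stated as 0.44. Freedman's formula at 90% power gives (1.960 + 1.282)² × (1.44/0.56)² = 69.5, so 70 events. With a mean event probability of 0.30, 70/0.30 = 233.3, or 117 per arm, and 117/0.8 = 146.25, so 147. The point does not depend on this calculation.

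**Attribution (illustration; every rate is an assumption).** Let p be the true SAE risk, equal in both arms, and a_T and a_C the fractions called related in the TIPSS and control arms.

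- Counted risk: p × a_T and p × a_C.
- Apparent risk ratio: (p × a_T)/(p × a_C) = a_T/a_C. The true risk cancels.
- Standard error of the log risk ratio: √[(1 − π_T)/(147π_T) + (1 − π_C)/(147π_C)], where π is the counted risk.
- Chance that the 95% CI excludes 1: Φ(z − 1.96) + Φ(−z − 1.96), with z = ln(RR)/SE.

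Example with p = 0.30, a_T = 0.40, a_C = 0.20: the counted risks are 0.12 and 0.06. SE = √(0.88/17.64 + 0.94/8.82) = √0.1565 = 0.396, and z = 0.693/0.396 = 1.75. The chance is about 0.418.

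| True risk, both arms | Called related, TIPSS | Called related, control | Counted, TIPSS | Counted, control | Apparent RR | Chance that CI excludes 1 |
|---|---|---|---|---|---|---|
| 30% | 40% | 40% | 12% | 12% | 1.00 | 0.050 |
| 30% | 40% | 30% | 12% | 9% | 1.33 | 0.133 |
| 30% | 40% | 20% | 12% | 6% | 2.00 | 0.418 |
| 50% | 40% | 40% | 20% | 20% | 1.00 | 0.050 |
| 50% | 40% | 30% | 20% | 15% | 1.33 | 0.202 |
| 50% | 40% | 20% | 20% | 10% | 2.00 | 0.645 |

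Swapping the last pair, with 20% called related after TIPSS and 40% in control, gives 0.20/0.40 = 0.50. The direction is set by the assumption, not by the design.

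**Ascertainment (illustration).** If the control arm captures a fraction c of the SAEs that TIPSS-arm reporting would capture over the 12 months, and true risks are equal, the apparent RR is 1/c.

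| c | Apparent RR | Chance that CI excludes 1 (true risk 30% to 50%) |
|---|---|---|
| 1.00 | 1.00 | 0.050 |
| 0.95 | 1.05 | 0.059 to 0.071 |
| 0.90 | 1.11 | 0.088 to 0.137 |
| 0.80 | 1.25 | 0.211 to 0.402 |

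The low values of c are hard to reach by this route. Since c refers to the whole 12-month count and the schedules differ only before 6 weeks, c = 0.80 would mean that a fifth of all control SAEs occurred early and were then missed by the 6-week report.

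**The case against.** Several counter-arguments carry weight.

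- **Most harms escape the problem.** A reader might infer that the whole comparison of harms is biased. It is not. Rebleeding (including banding-ulcer bleeding, a harm of the control treatment), ascites, encephalopathy, spontaneous bacterial peritonitis, hepatocellular carcinoma and renal dysfunction are compared without a relatedness judgement. Death and transplant form the primary outcome. This stands and limits the point to one secondary outcome.
- **Unattributed events are not lost.** It is tempting to say that they vanish from the trial. The Economic evaluation section has liver failure, intensive care admission, inpatient stays and readmissions collected prospectively, with no relatedness condition. They are collected there as resource use rather than as the SAE outcome, but they are collected.
- **The direction is not fixed.** One might infer that TIPSS must look worse. Banding and beta-blockers are also treatments to which events can be attributed, and the article expects control treatment to be modified for intolerance or SAEs. This stands.
- **Early control events can still be recorded.** The outcome window is 12 months in both arms, and a day 2–7 event falls within the period before the 6-week report. Nothing says that an SAE counts only if found at a scheduled contact. This stands and makes the schedule a secondary point.
- **The abstract may be shorthand.** It probably is. It does not show that an all-SAE outcome was intended, only that the two wordings should agree.
- **This is a condensed article.** Causality assessment, all-SAE recording and adjudication may be in the full protocol, so their absence here is no finding.

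What survives is the outcome definition itself, which the article states.

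**Conclusion.** The point holds in limited form. As listed, the SAE outcome depends on an unblinded judgement of relatedness that need not work alike for a discrete procedure and for ongoing usual care. It is open to bias; the documents do not show that it is biased. The size and direction are unknown. The range of 1.00 to 2.00 in the apparent risk ratio merely restates the assumed attribution fractions, and the bias is zero if attribution is equal in the two arms. The TIPSS-only 2–7 day safety report adds bias only if the control arm's 6-week report misses early events, which nothing in the article suggests will happen often. The primary outcome, the other harm outcomes and the sample size are untouched. The change is worth making because it is cheap and removes the relatedness judgement from the between-arm SAE comparison.

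**What to change.** 1. Define the compared safety outcome as all SAEs to 12 months after randomisation, regardless of relatedness, and use the same wording in the abstract and the outcome list.
2. Keep treatment-related SAEs as a supplementary summary, with relatedness reviewed blind to allocation where feasible.
3. Use the same early safety-reporting time point in both arms. In control this can be a notes review; the Doppler scan can stay TIPSS-only.

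The cost is one short extra form per control participant and a change of outcome wording. The trade-off is that an all-SAE count includes disease-related events that neither treatment causes, which adds noise and can pull a real treatment-related difference towards the null. That is the reason to keep the related-SAE summary beside it. The sample size does not change.

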### Schedule of assessments

Schedule of assessments is detailed in table 1.

**Table 1 T1:** Schedule of assessments

Assessment	Eligibility and randomisation	Baseline	2–7 days (TIPSS arm only)	6 weeks±7 days	6 months±7 days	12 months±7 days
Inclusion criteria*	x					
Exclusion criteria*	x					
Seek informed consent	x					
Relevant medical history taken	x					
Concomitant medication		x		x	x	x
Randomisation	x					
Full blood count		x		x	x	x
TIPSS procedure under fluoroscopic guidance†		x				
Renal function		x		x	x	x
Clotting profile	x			x	x	x
Liver function	x			x	x	x
Diagnostic endoscopy	x					
Standard clinical examination		x		x	x	x
Doppler ultrasound	x		x		x	x
Safety reporting		x	x	x	x	x
Quality of life questionnaires (EQ-5D-5L)		x			x	x
Child-Pugh Score ‡	x				x	x
MELD Score		x			x	x

Color significance HIghlight the assessment variable.

*Refer to text for inclusion and exclusion criteria.

†Early TIPSS arm only.

‡Child-Pugh Score is a minimisation variable.

EQ-5D-5L, EuroQol-5 Dimension-5 Level; MELD, Model For End-Stage Liver Disease; TIPSS, transjugular intrahepatic portosystemic stent–shunt.

### Statistical considerations

#### Sample size

The meta-analysis by Deltenre *et al* showed that early TIPSS results in an over 60% reduction in mortality compared with standard of care.^15^ However, we believe this is an overestimate when considering recent RCTs and propose a more conservative estimate.^10 14^ We have based our sample size on being able to detect a difference in transplant-free survival between two arms (standard care vs TIPSS) using a two-sided log-rank test. We have assumed a 1-year transplant-free survival rate in the standard care group of 60% and 80% in the TIPSS group (HR 0.44). To detect this difference with 90% power (alpha=0.05) and allowing for 20% attrition, we require 70 events across 294 participants (147 participants per arm).

#### Statistical analysis

A separate statistical analysis plan will provide a more comprehensive description of the planned statistical analyses. A brief outline of the planned analyses is given below.

The primary comparison groups will be composed of those randomised to standard of care versus those randomised to TIPSS. In the first instance, all analyses will be based on the intention-to-treat principle, that is, all participants will be analysed in the intervention group to which they were randomised irrespective of adherence to randomised intervention or protocol deviations. For all outcomes, appropriate summary statistics and differences between groups will be presented, with 95% CIs. Where possible, intervention effects will be adjusted for the minimisation variables as detailed earlier and baseline score (where appropriate). No adjustment for multiple comparisons will be made.

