
The trial by Dunne *et al* highlights the challenges in adherence to the 72-hour window for early TIPSS, with 23/29 patients (79%) actually having a TIPSS and only 13/23 receiving TIPSS within 72 hours, but all within 5 days. It is, however, worth noting that a previous UK RCT of TIPSS versus banding for secondary prevention of variceal rebleeding,^13^ where TIPSS was placed within 72 hours of acute bleeding in all patients, had similar results to the trial by Dunne *et al.*
14 However, the standard of care was not in keeping with current practice and TIPSS was done using bare stents. An important finding of all these RCTs is that rescue TIPSS was necessary in between 10% and 31% in the standard of care groups due to refractory rebleeding and was invariably associated with very poor outcomes.

Data from observational studies has fuelled the debate regarding patient selection for early TIPSS.^15–19^ While patients with Child-Pugh C disease appear to have improved survival following early TIPSS, this is not always the case for Child-Pugh B patients with active bleeding.^15–19^ An observational study also suggested that patients with a MELD Score of ≥19 are likely to benefit from early TIPSS,^17^ a finding confirmed by Lv *et al*.^18^ It is not clear from these studies if there is a maximum threshold of severity of liver disease beyond which there is no benefit from early TIPSS.

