### Eligibility criteria

To be eligible for REACT-AVB, a patient must be aged ≥18 years, have cirrhosis and present with an AVB with endoscopic haemostasis. Patients with failure to control bleeding as defined by Baveno VII criteria^4^ and those with occlusive portal vein thrombosis precluding TIPSS will be excluded. We did not include an upper age limit as there is no clear scientific basis for such an exclusion, for example, absolute age cut-off as a contraindication for TIPSS.^27^ Moreover, our patient and public representatives are in favour of age criteria being inclusive of all adults. Detailed inclusion and exclusion criteria are illustrated in figure 1.

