### Randomisation

Randomisation will be provided by Birmingham Clinical Trials Unit (BCTU) using a secure online system (available at: https://reactavb.bctu.bham.ac.uk/), thereby ensuring allocation concealment. Unique log-in usernames and passwords will be provided to those who wish to use the online system and who have been delegated the role of randomising patients into the trial as detailed on the REACT-AVB site signature and delegation log.

Participants with AVB will be randomised at the level of the individual, in a 1:1 ratio between early TIPSS and standard of care. A minimisation algorithm will be used within the online randomisation system to ensure balance in the intervention allocations over the following variables:

Child-Pugh Score (7–9/10–13).Airway intubation for endoscopy (yes/no).Antibiotics administered (yes/no) (prior to or within 24 hours of diagnostic endoscopy).Terlipressin administered (yes/no) (prior to or within 24 hours of diagnostic endoscopy).Active bleeding seen at diagnostic endoscopy (yes/no).Recruiting centre.

To avoid the possibility of the intervention allocation becoming predictable, a random element will be included in the randomisation algorithm.

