#### Primary outcome

The primary outcome will be compared between treatment groups using survival analysis methods. A Cox proportional hazard model will be fitted if the assumptions of proportionality are met, and an adjusted HR with a 95% CI will be presented. The p value relating to the intervention group parameter as generated by the model will be presented. Kaplan-Meier survival curves will be constructed for visual presentation.

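### The stated covariate set for the primary Cox model omits age and baseline MELD, which gives up some power at little saving

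*Protocol article*

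**What the plan says.** All references are to the protocol article.

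- **Statistical analysis** sets the adjustment rule for all outcomes: "Where possible, intervention effects will be adjusted for the minimisation variables as detailed earlier and baseline score (where appropriate").
- **Randomisation** lists the minimisation variables. The list opens with "Child-Pugh Score (7–9/10–13).Airway intubation for endoscopy (yes/no") and continues with antibiotics, terlipressin and active bleeding (each yes/no) and recruiting centre. Age and MELD are not on it.
- **Primary outcome** (under Statistical considerations) rests on this sentence, cut short here: "A Cox proportional hazard model will be fitted if the assumptions of proportionality are met, and an adjusted HR with a 95% CI will be". The reported p value comes from the same model.
- **Sample size** plans the comparison "using a two-sided log-rank test". Its survival inputs are stated as follows: "We have assumed a 1-year transplant-free survival rate in the standard care group of 60% and 80% in the TIPSS group (HR 0.44"). Error rates and loss to follow-up are then fixed: "with 90% power (alpha=0.05) and allowing for 20% attrition". The result is 70 events in 294 participants.
- **Eligibility criteria** admits adults of any age: "We did not include an upper age limit as there is no clear scientific basis for such an exclusion".
- **Table 1** places the MELD score and renal function in the Baseline column. Clotting and liver function are under Eligibility and randomisation.
- **Existing research and current practice** names MELD of 30 or more among the features of patients with high mortality. It also cites an observational study suggesting that "patients with a MELD Score of ≥19 are likely to benefit from early TIPSS".

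**The concern.** The covariate set matters because the trial's main estimate and test come from the adjusted model. As stated, that set is thin on prognosis. Its only liver-severity term is a two-level Child-Pugh band. The section on identification of patients says that everyone receives vasoactive drugs and antibiotics, so the antibiotic and terlipressin factors should vary little and explain little. The phrase about a baseline score does not naturally add anything here: it suits outcomes that are themselves scores (Child-Pugh, MELD, EQ-5D-5L), and transplant-free survival has no baseline value.

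In a Cox model, leaving out covariates that predict the outcome pulls the treatment hazard ratio towards 1 and costs power. That matters most if the true effect is smaller than planned, and the article's own evidence allows for this. The meta-analysis of four randomised trials gives a 1-year mortality relative risk of 0.76 (95% CI 0.51 to 1.14). Applied to 40% control mortality, that is 0.40 × 0.76 = 30.4%, or about 70% survival instead of 80%. The most recent UK trial found no difference in 1-year survival.

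**Working it through.** **Step 1. Reproduce the plan's figure.** Inputs from Sample size: HR 0.44, two-sided alpha 0.05, power 90%, survival 60% and 80%, attrition 20%.

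- Check of the HR: ln(0.80)/ln(0.60) = 0.437, stated as 0.44.
- Freedman events: [(1 + 0.44)/(1 − 0.44)]² × (1.960 + 1.282)² = 69.5, rounded up to 70.
- Mean event probability: (0.40 + 0.20)/2 = 0.30. Then 70/0.30 = 233.3, or 117 per arm.
- Attrition: 117/0.80 = 146.25, rounded up to 147 per arm, 294 in total.

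Both stated figures match, without any use of age or MELD. (Schoenfeld's formula would ask for 63 events; with 70 it gives 93% power.)

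**Step 2. Gain in closed form.** Keep Child-Pugh as a two-level factor (assumed HR 2, half the patients in each band). Represent what age and MELD add beyond it as a normal score with SD s on the log-hazard scale, so that exp(s) is its HR per SD. Hold marginal 1-year survival fixed and solve for the conditional treatment HR with and without the score. The equivalent event ratio is (log HR with score / log HR without)². Power follows as Φ[(1.96 + z of base power) × √ratio − 1.96].

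| Residual HR per SD (assumed) | Event ratio, 60% v 80% | Power from nominal 90% | Event ratio, 60% v 75% | Power from 80% |
|---|---|---|---|---|
| 1.28 | 1.023 | 90.6% | 1.026 | 81.0% |
| 1.49 | 1.061 | 91.6% | 1.068 | 82.5% |
| 1.82 | 1.144 | 93.4% | 1.160 | 85.5% |
| 2.12 | 1.233 | 94.9% | 1.256 | 88.1% |

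At the planned effect, the treatment HR moves from 0.430 without the score to 0.391 with it at the strongest setting. A Cox simulation with 234 patients (2,000 runs each) gives similar event ratios: 1.058 at HR per SD 1.49 and 1.137 at 1.82.

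**Step 3. Gain by simulating the whole trial.** Assumptions, none from the article: 20% attrition occurring in 294 patients, MELD SD 5.5 with correlation 0.6 to Child-Pugh, age SD 11 years, and three sets of prognostic strength (HR 1.05–1.11 per MELD point, 1.22–1.49 per 10 years of age, 1.16–1.28 per Child-Pugh point). There were 1,500 trials per scenario. Child-Pugh stays as the planned band, and only age and MELD are added.

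| True survival | Power, planned set → with age and MELD (three strengths) |
|---|---|
| 60% v 80% | gain of at most about 2 points |
| 60% v 75% | 77→79%, 80→84%, 79→87% |
| 60% v 72% | 58→60%, 58→65%, 61→69% |

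Event equivalents at 60% v 75%: [(1.96 + 0.806)/(1.96 + 0.739)]² = 1.05 for 77→79%, and [(1.96 + 1.126)/(1.96 + 0.806)]² = 1.245 for 79→87%.

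A separate simulation at 60% v 80% gave 95.0–97.1% rising to 95.8–98.8%. The gain in points is small there because power is already well above the nominal 90%: Freedman's formula is conservative at this HR, and patients lost part-way still contribute follow-up.

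**The case against.** The strongest reply is that nothing in the plan is wrong. Adjusting a minimised trial for its minimisation factors is sound, Child-Pugh is among them, and the sample size never relied on more. The section calls itself a brief outline, defers detail to a separate SAP and speaks of adjustment only where possible. All of that stands, and it limits the point to efficiency. It does not remove it: the article states an adjustment set, and a better one is available from data already scheduled. The SAP may already refine it.

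The size of the gain is also open to challenge. The article gives no hazard ratio or SD for age or MELD, so the range reflects the assumptions, and its low end is negligible. This stands.

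Three stronger readings are tempting and are not supported.

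- *The trial is underpowered.* Step 1 shows otherwise under the stated assumptions.
- *The planned analysis is biased or invalid.* The movement of the HR towards 1 is the usual difference between a less and a more conditional estimate, and the test remains valid.
- *The article shows that age and MELD are strong predictors.* It links MELD to mortality only at 30 or more. The threshold of 19 concerns who may benefit from TIPSS, and the remark on the age limit says nothing about prognosis.

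Lastly, Table 1 does not place MELD's renal input before allocation, and the Baseline column also holds the TIPSS procedure. The value therefore cannot be used without a timing rule.

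**Conclusion.** The point holds as a modest, low-cost improvement. The stated set for the primary Cox model leaves out age and baseline MELD and carries severity only as a two-level Child-Pugh band.

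At the planned 60% versus 80%, the gain is about 0–2 power points in simulations of the full trial. Counted from the nominal 90% by formula, it would be at most about 5 points. At 60% versus 75% it is about 1–8 points, equivalent to roughly 2–25% more events. These figures assume a residual HR per SD of about 1.3–2.1 for age and MELD together beyond Child-Pugh. If the residual value is weaker, for example because MELD overlaps heavily with Child-Pugh through bilirubin and clotting, the gain is close to nil. Direction is secure if the covariates are prognostic; size is not.

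**What to change.** In the Statistical analysis section and the SAP, before any comparative data are seen:

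1. Name age and baseline MELD as continuous covariates in the primary Cox model, alongside all the planned minimisation variables, with centre handled as already intended.
2. Define baseline MELD as the value from the last blood results before randomisation, with an explicit rule for the renal input.
3. Report the model with the minimisation variables only as a supporting analysis.

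The cost is mainly wording. There are two more terms in a model with about 70 events, the adjusted HR is conditional on slightly more covariates than now planned, and sites need a timing rule (possibly a small change to data collection) so that the renal result used for MELD predates allocation. Fixing the set now also avoids a later dispute over covariate choice in an open-label trial.
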